### Other collected data

The following data will be recorded for each infant: gestational age (GA), birth weight (BW), sex, Apgar score at 5 minutes, antenatal steroid treatment, CRIB II score [11], occurrence of pneumothorax, patent ductus arteriosus (PDA) and need of surgical closure, grade 3 to 4 intraventricular hemorrhage (IVH) [12], periventricular leukoma-lacia (PVL) [13], grade >2 retinopathy of prematurity (ROPand ROP requiring surgery [14], necrotizing enterocolitis (NEC) [15], sepsis [16], length of stay in neonatal intensive care unit (NICU) and hospital, and mortality. Patients will be discharged from the NICU to a lower level of care when they no longer need respiratory assistance other than oxygentherapy and central venous catheters.

### Sample size

We hypothesize that SLI maneuver might decrease the need for MV during the first 72 hours of life from 35% to 20%. We calculated that 138 newborns must be enrolled in each group to detect this difference as statistically significant with 80% power at a level of 0.05.

### Recruitment

Written and oral information will, whenever possible, be offered to parents prior to the birth of their child if there is a risk that the mother will have a preterm delivery and the infant is likely to be eligible. Informed written consent will be signed by both the parents and sufficient time will be allowed for consent. Non-Italian speaking parents will only be asked for their consent if an adult interpreter is available. Trust interpreter and link worker services will be used to support involvement of participants whose first language is not Italian. A senior investigator will be available at all times to discuss concerns raised by parents or clinicians during the course of the trial.

A monthly accrual report of the study will be sent to participating centers.

### Randomization

Infants at each unit will be assigned to a block (1st block: gestational age from 25^+0^ to 26^+6^ weeks; 2nd block: gestational age from 27^+0^ to 28^+6^ weeks) and randomly assigned to a treatment group in 1:1 ratio using automatically generated sealed opaque envelopes, which will be prepared at Careggi University Hospital, Florence, Italy, and then distributed to participating centers. Block size will be concealed to investigators to ensure treatment balance between the two arms of the study.

### Blinding

The study will not be blinded and the staff performing the study will also care for the infants later on. However, the decision to start MV will be made by clinicians other than the investigators involved in patient care and researchers assessing study end-points will be blinded to the nature of the study treatments.

To minimize bias, strict criteria and definitions will be maintained during the trial.

### SLI maneuver

Infants in the SLI group will undergo the following approach. After oropharyngeal and nasal suctioning, pre-ssure-controlled (25 cmH_2_O) inflation will be sustained for 15 seconds, using a neonatal mask and a T-piece ventilator, followed by the delivery of 5 cmH_2_O NCPAP. Patients will be observed for the following 6 to 10 seconds to evaluate their cardio-respiratory function. If respiratory failure persists (that is, apnea and gasping) and/or the heart rate is >60 and <100 bpm despite NCPAP, the SLI maneuver (again 25 cmH_2_O for 15 seconds) will be repeated. If the heart rate remains >60 and <100 bpm after the second SLI maneuver, the infant will be resuscitated following the current guidelines of the American Academy of Pediatrics (AAP) [17]. Moreover, if the heart rate remains <60 bpm the infant will be resuscitated following the current guidelines of the AAP [17], and a second SLI maneuver will be repeated when the heart rate increases to >60 and <100 bpm. Infants in the control group will be treated with delivery of 5 cmH_2_O NCPAP and will be assisted following the guidelines of the AAP [18].

All enrolled infants will be transferred to the NICU in NCPAP (PEEP at 5 cmH_2_O).

Neonatal care will be started with FiO_2_ of 0.21 to 0.40 in both the groups, in agreement with the local protocols. Respiratory support in the delivery room will be given using the same T-piece ventilator (Neopuff Infant T-Piece Resuscitator, Fisher & Paykel, Auckland, New Zealand), which is a pressure-limited mechanical device that supplies consistent peak inspiratory pressure (PIP) and PEEP, and is capable of delivering sustained inflation [7]. To avoid pressure leakage, a neonatal mask of appropriate size which adequately covers both the mouth and nostrils of infants will be used. The flow rate will be set at 8 to 10 l/min without changes during the resuscitation.

### Criteria for starting MV

In the delivery room, infants will be started on MV if they have not reached the goal of 70% SpO_2_ by 5 minutes [19] and 85% by 10 minutes of life [17] with a heart rate >100 bpm, despite NCPAP at 5 cmH_2_O. In the NICU, infants will be started on MV when the pH is <7.20 with PaCO_2_>65 mmHg, PaO_2_<50 mmHg with FiO_2_ ≥0.50 after surfactant treatment, or if infants have frequent episodes of apnea (>4 episodes in 1 hour or >2 episodes requiring bag-and-mask ventilation), despite adequate NCPAP (5 to 7 cmH_2_O) delivery and oxygenation. MV will be set to maintain a PaCO_2_ of 55 to 65 mmHg and 88 to 95% SpO_2_.

### Other aspects of respiratory support

To maintain an adequate SpO_2,_ infants with an FiO_2_ ≥0.40 will be treated with surfactant (200 mg/kg Curosurf, ChiesiPharmaceuticals, Parma, Italy) followed by the reinstitution of NCPAP as soon as vital signs are satisfactory (intubation-surfactant-extubation (INSURE) strategy). All infants who will need MV will be treated with surfactant and will then be gradually weaned from it. Additional doses of surfactant (100 mg/kg) will be given to infants, also through the INSURE strategy, at the discretion of the attending neonatologist.

Infants will be extubated, after a loading dose of caffeine citrate (20 mg/kg), when they meet all of the following criteria: FiO_2_<0.40, PaCO_2_<65 mmHg with a pH >7.20, MAP <7 cmH_2_O, hemodynamic stability and the absence of clinically significant patent ductus arteriosus.

### Data collection

All collected data will be obtained from the clinical records. They will be recorded on electronic data sheets designed for this study. Data will be entered by the local principal investigator on a web-based electronic case record form. Access to the form will be password protected and participants will be identified by trial number only.

Clinical information will be collected at the following times:

1. 1.At trial entry: eligibility, background information and randomization

2. 2.Following randomization: all data above listed in ‘Primary outcome measure’, ‘Secondary outcome measures’ and ‘Other collected data’ sections.

Further information will be collected on expected serious adverse events (SAEs).

### Statistical analysis

The primary efficacy analysis will be conducted on an intention-to-treat basis. Clinical characteristics of infants in the SLI and control groups will be described using mean values and SD, median value and range, or rate and percentage. Univariate statistical analysis will be performed using the Student’st-test for parametric continuous variables, the Wilcoxon rank-sum test for non-parametric continuous variables and the chi-square test for categorical variables. A *P*<0.05 will be considered statistically significant. SLI treatment and clinical characteristics which are most likely associated with the need for MV (gestational age, birth weight, antenatal steroids, CRIB score, INSURE procedure and hospital of birth) will be included in multiple logistic regression analysis to assess their independent role in predicting SLI success or failure. Effect estimates will be expressed as relative risk (RR) with profile likelihood-based 95% confidence limits.

An interim analysis is planned when 100 infants are enrolled (50 in each arm).

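### Randomisation is stratified by unit and gestational-age band, but no planned analysis makes valid use of the strata: the plain chi-square stays valid but conservative, and some efficiency is forgone

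*Protocol article*

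**What the plan says.** **Randomization.** "Infants at each unit will be assigned to a block", where the two so-called blocks are gestational ages 25+0 to 26+6 and 27+0 to 28+6 weeks. Infants are then "randomly assigned to a treatment group in 1:1 ratio" by sealed envelopes sent out to the centres. I read this as stratification by unit and by gestational-age band.

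**Sample size.** For a fall in need for MV from 35% to 20%, "138 newborns must be enrolled in each group", "with 80% power at a level of 0.05".

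**Statistical analysis.** Under univariate analysis, the test given for categorical data is "the chi-square test for categorical variables". SLI treatment and the characteristics thought most likely to be associated with need for MV "will be included in multiple logistic regression analysis". Those characteristics are "gestational age, birth weight, antenatal steroids, CRIB score, INSURE procedure and hospital of birth". The stated aim of the model is to find independent predictors of success or failure. Effects are to be reported as relative risks with profile-likelihood 95% limits, without saying which analysis supplies them.

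**The concern.** When allocation is balanced within strata that predict the outcome, the difference between arms varies less from trial to trial than the plain chi-square assumes. The test then rejects a true null less often than 5%, and precision that the design has already bought goes unused. The plan itself lists gestational age and hospital among the factors most likely to be associated with need for MV, so it expects the strata to matter.

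The logistic model does not fill the gap, because it conditions on INSURE:

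- Under Other aspects of respiratory support, INSURE is triggered by the infant's oxygen requirement, so it comes after the delivery-room intervention.
- Under Criteria for starting MV, the oxygenation criterion in the NICU is judged after surfactant.
- Under Secondary outcome measures, need for surfactant is itself an outcome.

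Adjusting for INSURE can therefore remove part of the SLI effect or distort it. The two analyses described thus leave a choice between one that ignores the strata and one that uses them alongside a post-randomisation variable.

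**Working it through.** **1. Inputs.** From the protocol article: 35% versus 20%, 138 per group, 80% power, level 0.05 (sides not stated), 1:1 allocation, strata of unit by two bands. Not in the article, so assumed: number of centres (10, equal in size), share of infants in the younger band (40%), and strength of the strata.

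**2. The plan's own figure.** Two-sided, pooled variance, no continuity correction, mean rate 0.275:

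n = [1.960·√(2·0.275·0.725) + 0.8416·√(0.35·0.65 + 0.20·0.80)]² / 0.15²
= [1.960·0.6315 + 0.8416·0.6225]² / 0.0225
= (1.2377 + 0.5239)² / 0.0225 = 137.9, so 138.

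This matches; power at 138 per group is 80.0%. Other versions do not match: 109 one-sided, 122 one-sided with continuity correction, 151 two-sided with continuity correction, 136 with unpooled variance. The trial is therefore sized for the unstratified comparison.

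**3. Why the plain test is conservative, by hand.** Take no treatment effect, an overall rate of 35%, and rates of 50% and 25% in the younger and older bands (odds ratio 3; 0.4·0.50 + 0.6·0.25 = 0.35).

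- Variance used by the chi-square: 0.35·0.65 = 0.2275.
- Variance between bands: 0.4·0.6·(0.50 − 0.25)² = 0.015.
- Variance that remains when the arms are balanced within bands: 0.2275 − 0.015 = 0.2125.
- Standard error used relative to the true one: √(0.2275/0.2125) = 1.035.
- True type I error: 2·[1 − Φ(1.960·1.035)] = 2·[1 − Φ(2.028)] = 4.3%.

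**4. Simulation.** 20,000 trials per scenario, equal arms within each stratum, marginal rates held at 35% and 20%. CMH is the Cochran-Mantel-Haenszel test. OR is the gestational-age odds ratio and SD the centre SD on the logit scale. Gains are taken before rounding.

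| Assumed strata | N | Power, chi-square | Power, CMH | Gain (points) | Type I, chi-square | Type I, CMH |
|---|---|---|---|---|---|---|
| Band only, OR 2 | 276 | 80.6% | 81.2% | 0.6 | 4.8% | 5.0% |
| Band only, OR 3 | 276 | 80.8% | 82.6% | 1.7 | 4.2% | 4.8% |
| Band only, OR 4 | 276 | 81.2% | 83.8% | 2.6 | 3.9% | 5.2% |
| 10 centres, strata not prognostic | 280 | 80.9% | 80.7% | −0.2 | 5.3% | 5.1% |
| 10 centres, OR 2, SD 0.3 | 280 | 81.6% | 82.4% | 0.8 | 4.5% | 4.7% |
| 10 centres, OR 2, SD 0.5 | 280 | 82.3% | 83.7% | 1.5 | 4.4% | 5.0% |
| 10 centres, OR 3, SD 0.5 | 280 | 82.7% | 85.0% | 2.3 | 3.9% | 5.0% |
| 10 centres, OR 3, SD 0.8 | 280 | 83.5% | 87.0% | 3.5 | 3.5% | 5.2% |
| 10 centres, OR 4, SD 1.0 (extreme) | 280 | 84.1% | 89.0% | 4.9 | 2.8% | 5.3% |

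N is 280 with 10 centres because stratum sizes are rounded. The 4.2% for the band-only OR 3 row agrees with the 4.3% found by hand. The unstratified standard error is about 0 to 5% too large for weak to moderate strata and 12% too large in the extreme row.

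A separate simulation, also at 35% versus 20% with 10 centres, covered OR 1.8 to 4.9 and SD 0.3 to 0.8. Chi-square power was 80 to 81.5%, the CMH gain was about 0 to 4 points, and chi-square type I error ran from 5.1% (weak strata) down to 3.2% (strong strata).

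**The case against.** The strongest reply is that nothing here is an error. The unstratified test does not inflate type I error and delivers the power the trial was sized for. Both stratification factors do appear in a planned model. A condensed article may leave the choice of primary model to the full plan. All of that stands, and the article's silence on which analysis is primary is not the point made here. What remains is that neither analysis it does describe fits the design.

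Four stronger readings are tempting, and the article does not support them.

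- **That the primary outcome is tested by the chi-square.** The test is listed for categorical variables in general and is not named as the primary test of need for MV.
- **That the reported confidence limits are too wide.** They are profile-likelihood limits, which are model-based, and the article does not tie them to an unadjusted table.
- **That planned power is lost.** A simulation with a fixed conditional odds ratio of 0.45, and band rates of 50%/25% or 55%/20%, puts chi-square power at 68 to 79%. Most of that shortfall comes from a smaller assumed effect. With 55%/20% and a centre SD of 0.8, the marginal rates become 35.4% and 22.3%, a difference of 13.1 points rather than 15. The ordinary two-proportion formula gives only 67% power for that, with no stratification involved.
- **That the logistic model is overfitted.** Expected events are 276·0.275 = 75.9. Nine hospital terms plus six others make 15 parameters, or 75.9/15 = 5.1 events each. This rests on 10 hospitals entered as fixed terms, and the article states neither.

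**Conclusion.** The point holds as an efficiency matter. The strata built into randomisation are not validly used by either analysis described: the chi-square ignores them, and the model that includes them also conditions on INSURE. The plain test is valid and keeps 80% power at 35% versus 20%. The cost is conservatism and unused precision: type I error of about 3 to 5% against a nominal 5%, and about 0 to 4 points of power forgone.

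The direction is certain if the strata predict need for MV. The size is not, because it depends on the assumed 10 centres, the odds ratio of 1.8 to 4.9 and the centre SD of 0.3 to 0.8. With weak strata the gain is close to nothing. I would class this as a free improvement, not the correction of a mistake.

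**What to change.** In Statistical analysis, state that the primary intention-to-treat analysis of need for MV within 72 hours is a Cochran-Mantel-Haenszel test with a common relative risk and its 95% interval, stratified by gestational-age band and centre. A relative-risk regression on treatment, band and centre, without INSURE, would serve as well. Describe the plain chi-square and the multivariable prediction model as supporting analyses.

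The cost is a few lines of text. Gestational age is listed under Other collected data and hospital of birth is already a planned covariate, so no new data and no change in sample size are needed. With 10 centres there would be 20 strata of about 276/20 = 14 infants. A stratum that ends up with infants in one arm only adds nothing to the stratified test, so a rule for pooling very small centres should be fixed in advance.

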### Primary outcome measure

The primary endpoint of this study will be the need for MV within the first 72 hours of life. Therefore, we will consider SLI a success if MV is not required and a failure if the infant needs MV. The need for MV is defined later under ‘Criteria for starting MV’.

We have chosen the need for MV during the first 72 hours of life as our primary outcome measure to maintain similarity with the main previous trial conducted on this issue [7].

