### Secondary outcome measures

1. Need for conventional or high frequency modes of ventilation in the first 3 hours of life.

2. Highest FiO_2_ and oxygentherapy duration.

3. Duration of NCPAP, need and duration of bi-level nasal continuous positive airway pressure (BiPAP) and NIMV.

4. Need and duration of conventional MV (synchronized intermittent mechanical ventilation (SIMV), synchronized intermittent positive pressure ventilation (SIPPV), pressure support ventilation (PSV) with or without with volume guarantee (VG)) or high frequency ventilation (HFV).

5. Duration of hospitalization.

6. Highest mean airway pressure (MAP) during MV.

7. Need and number of doses of surfactant.

8. Occurrence of mild, moderate and severe bronchopulmonary dysplasia (BPD) [10].

9. Death.

10. Death or severe BPD.

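### The regression for the primary outcome adjusts for INSURE, a treatment given after randomisation, so its SLI estimate is not the total effect of assignment and can be biased

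*Protocol article*

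**What the plan says.** All references are to the protocol article.

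- **Statistical analysis, the model.** The covariates listed beside SLI are "gestational age, birth weight, antenatal steroids, CRIB score, INSURE procedure and hospital of birth". Of SLI and these covariates taken together, the section states that they "will be included in multiple logistic regression analysis to assess their independent role in predicting SLI success or failure".
- **Primary outcome measure.** Success and failure are defined by the primary endpoint: "we will consider SLI a success if MV is not required and a failure if the infant needs MV". The regression's dependent variable is therefore MV within 72 hours.
- **Statistical analysis, the rest.** "The primary efficacy analysis will be conducted on an intention-to-treat basis". Categorical variables are compared by chi-square test. The sentence directly after the regression reads: "Effect estimates will be expressed as relative risk (RR) with profile likelihood-based 95% confidence limits".
- **Other aspects of respiratory support.** Infants whose FiO2 is at or above 0.40 "will be treated with surfactant (200 mg/kg Curosurf" and so on), and are then returned to NCPAP. This is the INSURE strategy. Further doses are left to the neonatologist.
- **Secondary outcome measures, item 7.** "Need and number of doses of surfactant".
- **Criteria for starting MV.** In the NICU the oxygenation limit applies "after surfactant treatment, or if infants have frequent episodes of apnea"; the apnoea criterion that follows carries no such condition.
- **SLI maneuver.** SLI is given in the delivery room, straight after suctioning.

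**The concern.** Adjusting for a baseline covariate does not disturb a randomised comparison. Adjusting for something that happens after randomisation, and that the treatment may alter, does.

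The article expects SLI to alter it. The Background says SLI with PEEP should improve gas exchange and reduce the need for respiratory support, and the Abstract counts surfactant as respiratory support. If SLI lowers oxygen need, fewer SLI infants reach the INSURE trigger.

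Two things can then go wrong in the adjusted model:

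- **Part of the effect is removed.** Any benefit that SLI brings by keeping infants off the path through INSURE is held constant and disappears from the SLI term.
- **The arms stop being comparable.** Sicker infants are more likely both to get INSURE and to be ventilated. If SLI spares INSURE for the milder cases, SLI infants who still get it are sicker on average than control infants who get it. The same holds among infants who do not get it. SLI then looks worse than it is.

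At stake is whether the adjusted RR, if that is the one reported, answers the question for which the trial was randomised.

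**Working it through.** **1. Order of events.** Randomisation, then SLI or NCPAP in the delivery room, then INSURE if FiO2 reaches 0.40, then MV if the criteria are met. INSURE lies between assignment and outcome. Gestational age, birth weight, antenatal steroids and hospital of birth are all fixed before the manoeuvre.

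**2. The plan's own figure.** The Sample size section gives 35% against 20%, 80% power and a 0.05 level. Taking the test as two-sided, with pooled variance and no continuity correction:

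n = [1.96 × √(2 × 0.275 × 0.725) + 0.8416 × √(0.35 × 0.65 + 0.20 × 0.80)]² / 0.15²
= (1.2377 + 0.5239)² / 0.0225 = 137.9, so 138 per group.

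This matches the article. It is an unadjusted comparison of two proportions, so the sample size does not depend on the regression. The planned total effect is RR 0.20/0.35 = 0.57.

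**3. What adjustment for INSURE can do.** The article gives no INSURE rate and no association of INSURE with SLI or with MV, so these are assumptions:

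- logit P(INSURE) = a × SLI + s × U
- logit P(MV) = m + b × SLI + c × INSURE + s × U

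U is unmeasured severity (standard normal), 50% of controls get INSURE, and m is set so that 35% of controls are ventilated. The adjusted RR comes from a logistic model with SLI and INSURE: predicted risks with SLI set to 1 and to 0 are averaged over the pooled INSURE distribution, and their ratio is taken.

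*Scenario A by hand* (a = −1, s = 0, b = 0, c = 1.5; SLI acts only through INSURE). Solving for m gives MV risks of 0.189 without INSURE and 0.511 with it, in both arms.
- Controls: 0.50 × 0.189 + 0.50 × 0.511 = 0.350.
- SLI arm, INSURE use 1/(1 + e) = 0.269: 0.731 × 0.189 + 0.269 × 0.511 = 0.276.
- True RR = 0.276/0.350 = 0.79. Within each INSURE stratum the risks are equal, so the adjusted RR is 1.00.

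*Scenario C by stratum* (a = −1, s = 1.5, b = 0, c = 0; SLI has no effect on MV). INSURE use is 50% in controls and 33% with SLI.

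| | Control MV | SLI MV |
|---|---|---|
| No INSURE | 21.6% | 25.6% |
| INSURE | 48.4% | 54.1% |
| All | 35.0% | 35.0% |

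SLI looks worse in both strata although the overall risks are equal. The adjusted RR is 1.14 (odds ratio 1.25).

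*All scenarios:*

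| Scenario | INSURE, control / SLI | True RR | Adjusted RR |
|---|---|---|---|
| A: effect only through INSURE | 50% / 27% | 0.79 | 1.00 |
| B: A plus a direct effect (b = −0.5) | 50% / 27% | 0.56 | 0.72 |
| C: no effect on MV, shared severity | 50% / 33% | 1.00 | 1.14 |
| D: C plus a direct effect (b = −1.1) | 50% / 33% | 0.55 | 0.65 |
| E: D, but SLI does not change INSURE (a = 0) | 50% / 50% | 0.55 | 0.55 |
| F: shared severity, INSURE protective (b = −1.2, c = −1) | 50% / 33% | 0.56 | 0.59 |

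These values come from numerical integration; simulations of 400,000 infants per scenario agree to within about 0.01. In E the odds ratio still moves, from about 0.45 to 0.42, because odds ratios are not collapsible. That is not bias, which is why the comparison is made on the RR scale.

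**The case against.** The best defence is that the regression is not the primary analysis. The section opens with intention to treat and names a chi-square test, the sample size is that of an unadjusted comparison, and the regression's stated aim sounds prognostic. Most of this stands. A reader might infer that the trial's main result is biased; the article does not support that, because the unadjusted comparison never conditions on INSURE.

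The defence does not clear the model, however. SLI is one of the terms whose independent role is to be reported. The next sentence promises RRs with profile-likelihood limits, which come from a fitted model, and this regression is the only one described. An SLI-only model could also supply them, but the article does not say so. The source of the reported RR is left open.

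Further limits that stand:

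- **Bias is possible, not certain.** It requires SLI to change INSURE use; scenario E shows essentially none otherwise.
- **The sizes rest on assumptions.** The planned model also contains birth weight, antenatal steroids, CRIB score and hospital, which might absorb some of the severity behind scenarios C, D and F.
- **INSURE is not itself a listed secondary outcome.** Item 7 is need for and doses of surfactant, which all ventilated infants also receive. The two are closely tied but not the same variable.
- **Delivery-room MV.** A reader might infer that an infant ventilated there cannot have had INSURE first. No section says so, and nothing here depends on it.
- **CRIB score.** A reader might infer the same fault. The article does not show when the score is taken, so no finding is made.

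**Conclusion.** The point holds for the adjusted model. As written, the regression conditions on a treatment given after randomisation that SLI may change and that is tied to surfactant need and to the NICU oxygenation criterion for MV. Its SLI term does not estimate the total effect of assignment and should not be reported as such.

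The article cannot settle how large the distortion would be. Across the illustrative scenarios it runs from none, when INSURE use is equal in the arms, to complete loss of a real effect or an apparent harm of 14% in relative terms where there is none. In every scenario where SLI lowers INSURE use, the adjusted RR is less favourable to SLI than the true one. That direction belongs to the assumptions chosen and is not a general result.

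The unadjusted intention-to-treat comparison, the 138 per group and the data collection are untouched. This is not a detail left to an analysis plan: the covariate list is stated, and one entry in it is wrong for estimating the SLI effect.

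**What to change.** In the Statistical analysis section:

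1. Remove the INSURE procedure from any model used to estimate the SLI effect.
2. Adjust only for covariates fixed before the manoeuvre: gestational age, birth weight, antenatal steroids and hospital of birth.
3. Name the one analysis that supplies the primary RR and its limits, either the unadjusted or the baseline-adjusted intention-to-treat analysis.
4. Report INSURE and surfactant use by arm as outcomes.
5. If a model containing INSURE is kept, label it exploratory or prognostic, and state that its SLI term is not the treatment effect.

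The cost is a few lines of text. No extra data or infants are needed, and the design stays at 138 per group with 80% power. The article reports that recruitment is under way, so the change should be dated and made before outcomes by arm are seen, including at the interim analysis planned at 100 infants.

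### Relative risks with profile-likelihood limits are promised, but the only model named is logistic regression, and no step leads from its odds ratios to an adjusted relative risk

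*Protocol article*

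**What the plan says.** Three parts of the protocol article bear on this.

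- **Endpoint.** Under Primary outcome measure the endpoint is binary: "we will consider SLI a success if MV is not required and a failure if the infant needs MV".
- **Planning rates.** Under Sample size, the hypothesis is that the "SLI maneuver might decrease the need for MV during the first 72 hours of life from 35% to 20" per cent, and "138 newborns must be enrolled in each group to detect this difference as statistically significant with 80% power at a level of 0.05".
- **Analysis.** Under Statistical analysis, univariate comparisons include "the chi-square test for categorical variables". SLI and six characteristics (gestational age, birth weight, antenatal steroids, CRIB score, INSURE and hospital of birth) "will be included in multiple logistic regression analysis to assess their independent role in predicting SLI success or failure". The sentence straight after that gives the reporting scale: "Effect estimates will be expressed as relative risk (RR) with profile likelihood-based 95% confidence limits".

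No log-binomial model, Poisson model or standardisation step is named. The text does not say whether the logistic model takes MV or its absence as the event.

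**The concern.** A logistic model is linear in the log odds. Its exponentiated treatment coefficient is an odds ratio, and profiling its likelihood for that coefficient gives limits for an odds ratio. An odds ratio approximates a relative risk only when the outcome is rare, and this trial plans on MV in a fifth to a third of infants.

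Two adjacent sentences therefore pair a model with an effect measure that the model does not return directly. An analyst who follows them literally could take the exponentiated coefficient and its limits from the logistic output and head the column RR. Clinicians and meta-analysts would then read a larger reduction in MV than the data show, with an interval that is also on the wrong scale. The matter is one of estimation and reporting.

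**Working it through.** **Inputs.** MV rates of 35% (control) and 20% (SLI), 138 per arm, 80% power and level 0.05, all from Sample size; 1:1 allocation from Randomization.

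**1. The plan's own figure.** The usual two-proportion formula, two-sided and without continuity correction, is

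n = [z₀.₉₇₅ √(2 p̄ q̄) + z₀.₈₀ √(p₁q₁ + p₂q₂)]² / (p₁ − p₂)²

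with p̄ = (0.35 + 0.20)/2 = 0.275. This gives [1.960 × √0.39875 + 0.842 × √0.3875]² / 0.15² = 137.9, so 138 per arm, which matches the protocol. Power at 138 per arm is 0.800. Sidedness is not stated; a one-sided test would need 109. The calculation compares two proportions and does not depend on whether an RR or an OR is reported later.

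**2. The two measures at the planning rates.**

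- RR = 0.20 / 0.35 = 0.571, a relative reduction of 43%.
- OR = (0.20/0.80) / (0.35/0.65) = 0.250 / 0.538 = 0.464, which taken for an RR is a reduction of 54%.
- Applied to the 35% control rate, an RR of 0.464 would imply an SLI rate of 0.35 × 0.464 = 0.1625, about 16%, where the planned rate is 20%.

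**3. Other control rates (assumed range, RR held at 0.571).**

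| Control rate | OR |
|---|---|
| 20% | 0.52 |
| 30% | 0.48 |
| 35% (plan) | 0.46 |
| 40% | 0.44 |
| 50% | 0.40 |

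The gap is present throughout and widens as MV becomes more common.

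**4. Limits, in an illustrative unadjusted result.** Take 28/138 (20.3%) on SLI against 48/138 (34.8%) on control. Inverting the likelihood ratio of the two-binomial model gives these profile-likelihood 95% limits:

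- RR = 28/48 = 0.58 (0.38 to 0.86)
- OR = (28/110)/(48/90) = 0.48 (0.27 to 0.82)

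The estimate and both limits move away from 1 on the odds scale. Both intervals exclude 1, so the significance conclusion is the same.

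**5. Which event is modelled.** With absence of MV as the event, RR = 0.80/0.65 = 1.23 and OR = 1/0.464 = 2.15. The odds ratio merely inverts when the event is switched, but the relative risk changes to a different quantity, and the distance between the two is much larger for the commoner event.

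**6. What cannot be computed.** All figures above are unadjusted. The adjusted odds ratio depends on how strongly the covariates predict MV, and the document gives no information on that.

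**The case against.** The article commits to the RR, which is the preferable measure here, and nowhere says that an odds ratio will be reported or relabelled. The RR sentence is general and may not refer to the logistic model at all, since that model reads partly as an analysis of prognostic factors. An RR with profile-likelihood limits needs no logistic fit: step 4 obtained one from the two-arm counts alone. An adjusted RR can be derived from a logistic fit by marginal standardisation. Finally, a condensed article can leave such detail to a full protocol or analysis plan that is not shown.

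Much of this stands. A reader might infer that the named model can never yield an RR, or that the trial will overstate the benefit. The document supports neither reading: routes to an RR exist, and the overstatement requires a labelling error that the text does not announce.

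What remains is the adjusted effect. The article does more than leave detail out. It names a model and, in the next sentence, a measure and an interval method that this model gives only for odds ratios. Standardisation is not named, and its limits normally come from the delta method or bootstrap, so even that route would not meet the sentence as written.

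**Conclusion.** The point holds as a mismatch between stated methods for the adjusted effect. If the exponentiated logistic coefficient were reported as the RR, then at the planning rates a 43% reduction (RR 0.571) would read as about 54% (OR 0.464). This rests on the protocol's 35% and 20%, on no adjustment, and on the mislabelling actually taking place; the size for the adjusted model is unknown.

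The unadjusted RR from the two-arm table, the chi-square test, the sample size of 138 per arm, and hence power and type I error, are not affected. It should be corrected before analysis because the correction is cheap, but it does not threaten the validity of the primary test.

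**What to change.** Amend the Statistical analysis section as follows.

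- **Unadjusted effect.** Report the RR and the risk difference for MV within 72 hours from the two-arm comparison. Profile-likelihood limits for this RR are available from the binomial likelihood.
- **Adjusted effect.** Name one route to the RR. One option is a log-binomial model with profile-likelihood limits, with Poisson regression and robust standard errors as the pre-stated fallback if it does not converge, which is possible with hospital of birth among the covariates. The other is to keep the logistic model and report the marginally standardised RR with delta-method or bootstrap limits.
- **If neither is wanted.** Label the logistic results as odds ratios.
- **Event.** State that need for MV, not its absence, is the modelled event.

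The cost is a few sentences of analysis text and a different model call or one post-estimation step. Data collection, design and sample size do not change. The downside is that under the Poisson or standardised route the adjusted limits are no longer profile-likelihood limits, so the sentence on limits has to be reworded to match.
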